# A prospective observational study to assess clinical decision-making, prognosis, quality of life and satisfaction with care in patients with relapsed/refractory multiple myeloma: the CLARITY study protocol

**DOI:** 10.1186/s12955-018-0953-4

**Published:** 2018-06-18

**Keywords:** Multiple myeloma, Quality of life, Fatigue, Satisfaction with care, Survival, Prognosis

## Abstract

**Background:**

Treatment decision-making in patients with relapsed/refractory multiple myeloma (RRMM) is challenging for a number of reasons including, the heterogeneity of disease at relapse and the number of possible therapeutic approaches. This study broadly aims to generate new evidence-based data to facilitate clinical decision-making in RRMM patients. The primary objective is to investigate the prognostic value of patient self-reported fatigue severity for overall survival.

**Methods:**

This multicenter prospective observational study will consecutively enroll 312 patients with multiple myeloma who have received at least 1 prior line of therapy and are considered as RRMM according to the International Myeloma Working Group (IMWG) criteria. Eligible RRMM participants will be adults (≥ 18 years old) patients and will be enrolled irrespective of comorbidities and performance status. At the time of study inclusion, data to calculate the frailty score are to be available. Patients will be followed up for 30 months and patient-reported outcome (PRO) assessment is planned at baseline and thereafter at 3, 6, 12, and 24 months. The following PRO validated questionnaires will be used: the European Organisation for the Research and Treatment of Cancer Quality of Life Questionnaire-Core 30 (EORTC QLQ-C30), the EORTC QLQ-MY20 and the EORTC QLQ-INFO25. Satisfaction with care and preference for involvement in treatment decisions will also be evaluated. Clinical, laboratory and treatment related information will be prospectively collected in conjunction with pre scheduled PRO assessments. Cox regression analyses will be used to assess the prognostic value of baseline fatigue severity (EORTC QLQ-C30) and other patient-reported health-related quality of life parameters.

**Discussion:**

Clinical decision-making in RRMM is a challenge and outcome prediction is also an important aspect to enhance personalized treatment planning. Given the paucity of PRO data in this population, this prospective observational study aims to provide novel information that may facilitate patients’ management in routine practice.

**Trial registration:**

This trial is registered as identifier NCT03190525.

## Background

Over the last decade, the introduction of newer targeted therapies has dramatically improved survival in Multiple Myeloma (MM) [1]. However, the identification of the “best” therapeutic approach for MM remains a major clinical challenge. Despite the efficacy of the novel agents, the occurrence of relapse or progression is inevitable for the majority of MM patients, including those who respond to first-line therapies. Therefore, the treatment of relapsed/refractory multiple myeloma (RRMM) presents unprecedented challenges due to the variety of treatment options on one side and the heterogeneity of diseases at relapse on the other, with the absence of clearly defined biological-based recommendations [2]. The choice of salvage therapy for patients with RRMM requires a careful evaluation of possible achievable clinical benefits and potential toxicities of treatments that might negatively impact on patients’ health related quality of life (HRQOL). In this scenario, the evaluation of patient-reported well-being and symptoms becomes a critical component of patients’ care management.

Despite the physicians’ awareness of the importance of HRQOL information in the care management of RRMM patients, a recent systematic review of the literature indicates a dearth of information in this area [3]. To our knowledge, the few studies that have included HRQOL or other patient-reported outcomes (PRO) data have been mainly conducted in newly diagnosed MM patients enrolled in randomized controlled trials (RCTs) [4].

### Rationale and clinical significance

The choice of treatment for MM patients has been traditionally focused on chronologic age and performance status, as surrogate markers for frailty [5]. Predicting outcomes in this population is critical and recent data has pointed out the limitations of traditional prognostic indicators, by emphasizing the role of geriatric assessment [6]. Palumbo and colleagues [6] demonstrated that geriatric assessment (i.e., the Katz Activity of Daily Living [ADL] [7], the Lawton Instrumental Activity of Daily Living [IADL] [8] and the Charlson Comorbidity Index [CCI] [9]) adds independent prognostic information for risk of death, progression, adverse events and treatment discontinuation regardless of type of therapy and the International Staging System (ISS) in newly diagnosed MM patients. Based on this key finding, Palumbo and colleagues developed the frailty score system [6] which combines factors such as age, comorbidities, cognitive and physical conditions of patients. Importantly, the International Myeloma Working Group (IMWG) proposed this score for the measurement of frailty in the treatment decision-making process thus widely supporting its use in routine practice (http://imwg.myeloma.org).

Although this important evidence indicates the need to enlarge the spectrum of prognostic factors that are considered relevant in MM patients, the frailty score does not include PROs, so as defined by the US Food and Drug Administration (FDA) [10]. A novel finding in the science of prognostication in oncology has been the evidence that PROs, such as symptoms or functional limitations, could also provide prognostic information for survival or other clinical outcomes in patients with advanced disease [11, 12].

Therefore, based on this compelling evidence stemming from the scientific literature, we will primarily investigate the prognostic value of baseline PROs for overall survival, beyond the frailty score [6], to possibly devise a patient-centric frailty score for RRMM patients. Although the frailty score was developed in newly diagnosed (elderly) patients enrolled in RCTs, and we are aware of the differences with the population that we will be enrolled in our study, it is possible that the prognostic value of this score might also hold true in a population that, per se, is even more frail than the study in which this score was developed [6]. The identification of PROs with independent prognostic value in RRMM has the potential to provide a strong rationale for a more patient-centric approach in routine practice. For example, it would greatly support the inclusion of a standard PRO assessment at the time of deciding type of salvage therapy. Based on previous findings in MM patients [13, 14] and in patients with other advanced hematologic malignancies [15], self-reported fatigue will be regarded as the primary outcome for prognostic factor analyses in this study. Furthermore, in a second instance, other PROs will also be investigated to determine whether they provide more accurate prognostic information than fatigue.

Another broad objective of CLARITY is that of generating data that may facilitate physicians to more effectively communicate with their patients and to better respond to individual needs and preferences. In situations for which several different treatment options are available, as it is the case for salvage therapies, and the choice of strategy depends on individual patient characteristics and preferences, shared decision making has been advocated [16, 17]. Shared decision making between patients and physicians may result in a variety of benefits, including increased patient satisfaction and improved clinical outcomes [18–20]. Ideally, patients should be encouraged to participate in decision-making with accurate knowledge about the risks and benefits of all the potential treatment options [21]. However, empirical work suggests that a collaborative treatment strategy might not be ideal for all patients [22, 23], for example, in older patients with more advanced diseases and reduced health conditions [24, 25]. Therefore, physicians should empathetically invite patients to engage to the maximum extent they desire in making treatment decisions [26]. Understanding the extent to which RRMM desire to be involved in making treatment decisions and how this perception is concordant with the understanding of their physicians is important to lay the groundwork for the development of more effective communication strategies. The majority of studies in this area have focused on breast cancer patients [27, 28] and other cancer populations [22] and there is a dearth of information on this topic for patients with MM. The very few studies that have examined this issue in MM patients have been limited by small sample size [29] hampering definitive conclusions.

In addition, previous studies have shown that patient with advanced hematologic malignancies highly value HRQOL issues and pointed out the importance of investigating how patient’s HRQOL relate to treatment choices [21]. The emphasis placed by physicians on HRQOL considerations, when considering various alternatives, is unknown as is whether it is different from the emphasis placed on this issue by their patients. Do RRMM patients value HRQOL issues more than their treating physicians when considering alternative treatments? Although it has been hypothesized that older adults with MM may prioritize HRQOL issues over other traditional clinical endpoints [30], there is currently little evidence-based information and research efforts are needed in this area.

The challenge of conveying prognostic information on survival is another challenge often addressed in this setting. Physicians often face difficulties in prognostic discussions with their patients and this is particularly true in the setting of advanced cancer populations with poor prognosis [31]. Therefore, another objective of this study is to assess the proportion of RRMM patients who seeks this information and try to identify socio-demographic and clinical factors associated with desire for prognostic information.

Finally, satisfaction with information provision will also be examined in this project, as an important component of the clinical decision-making process. Patients should be offered high-quality information about their disease and possible treatments options, including the short-term and long-term consequences of treatment.

Patient information is a crucial component of cancer care and rehabilitation [32]. For example, there is some evidence that patients who are well-informed about their cancer report reduced level of psychological burden, improved HRQOL outcomes and satisfaction with care [33]. Information can reduce anxiety, help develop coping skills and enhance recovery [34]. Satisfaction with information provision has been shown to be associated with improved HRQOL outcomes in some cancer populations [35], but this relationship has not been investigated in RRMM patients receiving modern therapies.

### Aims

The primary objective is overall survival (OS) as predicted by baseline self-reported fatigue severity (European Organisation for Research and Treatment of Cancer Quality of Life Questionnaire-Core 30) independently from other known prognostic factors for OS.

The secondary objectives are:to devise a patient-centric frailty score for RRMM patients;to investigate the prognostic value of the frailty score in the setting of RRMM;to investigate HRQOL over time (outcome measures: EORTC QLQ-C30 and QLQ-MY20) by type of treatment and examine factors that contribute the most in maintaining baseline HRQOL levels;to investigate relationship between satisfaction with information provision (outcome measure: EORTC INFO-25) and HRQOL outcomes (outcome measures: EORTC QLQ-C30 and QLQ-MY20);to assess patients’ preferences for involvement in treatment decision-making and the relationships between preferences and patient characteristics.

## Methods/design

### Study design and logistics

This is a multi-center international (Italy and UK) prospective observational study lead by the GIMEMA (Gruppo Italiano Malattie EMatologiche dell’Adulto). All patients enrolled in this study will be followed-up for 30 months from date of registration regardless of their compliance with PRO assessments at pre-scheduled time points. All data will be centrally collected and analyzed at the GIMEMA Data Center, in Rome (Italy). The GIMEMA Data Center will set up all the relevant administrative materials to be sent out to all participating Centers. Data in this study will be collected through a state of the art web-based data management system: REDCap [36].

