#### Follow-up CRF

The Follow-up CRF should be completed by physicians at 3, 6, 12, 24 and 30 months. Except for the evaluation at 30 month, these timepoints are in conjunction with PRO assessments. Data to be collected includes: status of patient (dead, alive or lost to follow-up/date of last follow up, date of progression and date of death), disease and treatment related complications, ECOG Performance status, and treatment discontinuation, so as previously defined in the report by Palumbo and colleagues [6]. Adverse events will also be recorded according to the NIH-defined common toxicity criteria CTCAE (Common Terminology Criteria for Adverse Events) version 4.0.

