### Statistical considerations

#### Sample size determination

Based on previous evidence in MM patients [13, 14], the EORTC QLQ-C30 fatigue scale was used to calculate sample size and considered as the primary outcome in this study. We performed a calculation in order to detect, at least, a hazard ratio (HR) of 1.11 for overall survival, for each 10-points increase (i.e. worse score) on the baseline fatigue scale, assuming a baseline standard deviation of 29 points [43]. Based on previous studies and on clinical grounds [44], we also assumed a minimum event rate of 35% during the study and considered a follow-up of 30 months from date of enrolment. Allowing for an alpha error of 0.05 and a power of 90%, the calculated sample size for this group is 296 patients. However, estimating an overall 5% of patients not evaluable for whatever reason, the actual sample size required is 312 patients.

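### The stated sample-size inputs need about 115 deaths, but 296 patients at 35% give about 104 (87% power, not 90%); a common closing date for survival would recover the difference

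*Protocol article*

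**What the plan says.** Sample size determination (protocol article) plans to detect "a hazard ratio (HR) of 1.11 for overall survival, for each 10-points increase (i.e. worse score) on the baseline fatigue scale". The spread of fatigue scores enters the calculation as a further input, with the authors "assuming a baseline standard deviation of 29 points". On events it says "we also assumed a minimum event rate of 35% during the study", and for the horizon the authors "considered a follow-up of 30 months from date of enrolment". The error rates are given as "Allowing for an alpha error of 0.05 and a power of 90" per cent, with no sidedness. The result is that "the calculated sample size for this group is 296 patients", raised to 312 for 5% non-evaluable. No required number of deaths is stated.

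Follow-up is described consistently. Under Study design and logistics all patients "will be followed-up for 30 months from date of registration". Under Follow-up CRF, the form that carries vital status and date of death, "The Follow-up CRF should be completed by physicians at 3, 6, 12, 24 and 30 months". Trial status puts the start of recruitment at November 2017 and its approximate end at November 2018. The last PRO assessment is at month 24.

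**The concern.** The primary objective is a Cox analysis of overall survival, and its power depends on the number of deaths. Two features of the plan bear on that number.

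- The stated sample size does not follow from the stated inputs. It is about 10% too small for the power claimed.
- Survival collection ends at each patient's own month 30. The study itself must stay open until about May 2021 for the last enrolee, so a patient registered in November 2017 could supply up to 42 months of survival but is scheduled to supply 30.

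The first feature overstates the power of the primary analysis. The second passes over an inexpensive way to make up the shortfall. The margin matters because fatigue must show value independent of the frailty score and established factors, and Sample size determination states no allowance for correlation between fatigue and those covariates.

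**Working it through.** **Inputs** (Sample size determination unless noted): HR 1.11 per 10 points, so θ = ln(1.11) = 0.1044; SD 29 points = 2.9 ten-point units; event proportion 35% (a minimum); power 90%; alpha 0.05, taken here as two-sided; 296 evaluable, 312 enrolled. Accrual is about 12 months (Trial status).

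**1. Trying to reproduce 296.** For a continuous covariate in a Cox model, D = (z_α + z_power)² / (SD × θ)² and N = D / event proportion.

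- D = (1.960 + 1.2816)² / (2.9 × 0.1044)² = 114.7 deaths, so N = 114.7 / 0.35 = 327.8, or 328. The plan says 296.
- One-sided alpha: D = 93.5, N = 268. This does not match either.
- Using 0.11 itself as the log hazard ratio: D = 103.3, N = 295. This nearly matches and corresponds to a hazard ratio of about 1.116.
- An unrounded HR of 1.115: D = 105.4, N = 301. This is also close.
- The allowance step is correct: 296 / 0.95 = 311.6, or 312.

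**2. Power of the stated size at HR 1.11.** Power = Φ(√D × SD × θ − 1.960).

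| Patients | Event proportion | Deaths | Power |
|---|---|---|---|
| 296 | 35% | 103.6 | 86.9% |
| 312, all evaluable | 35% | 109.2 | 88.5% |
| 296 | 38.8% | 114.8 | 90.0% |
| 328 | 35% | 114.8 | 90.0% |

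The last row keeps the fixed 30-month follow-up and still reaches 90%.

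**3. Effect of a common closing date.** Assumptions, not stated in the article: 35% dead at 30 months, no loss to follow-up, accrual over 12 months, and the same fatigue effect out to 42 months.

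- Constant hazard: λ = −ln(0.65) / 30 = 0.01436 per month.
- Uniform accrual makes follow-up uniform on 30 to 42 months. Event proportion = 1 − (e^(−30λ) − e^(−42λ)) / (12λ) = 40.3%. Deaths = 296 × 0.403 = 119.3; power 91.1%.
- Weibull hazards with uniform accrual: shape 0.7 gives 114.4 deaths and 89.9%; shape 1.3 gives 124.3 deaths and 92.1%.
- Accrual rising linearly over the 12 months, constant hazard: mean follow-up is 34 months and the event proportion about 38.6%, so about 114 deaths and 89.9% power.

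**4. Sensitivity to adjustment.** If the other covariates explain a share R² of the variance of fatigue (an assumption, tried from 0.1 to 0.3), the requirement becomes 114.7 / (1 − R²), or 127 to 164 deaths. Power is then 83% to 73% with 103.6 deaths, and 88% to 79% with 119.3.

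**The case against.** A reader might infer that stopping at a personal month 30 is what leaves 104 deaths where 115 are needed. The documents do not support this. The 30-month horizon is part of the sample-size calculation and is already reflected in the 35%; the gap comes from a sample size that does not follow from its inputs.

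A reader might also infer that observed survival is thrown away. No censoring or cut-off rule is stated. Survival after month 30 is simply not scheduled for collection, and censoring conventions may properly sit in a document not shown.

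Other points against:

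- The 35% is called a minimum, so 104 deaths is a lower planning value and not a forecast. This stands: 38.8% in 296 patients would suffice. But 35% is also the figure on which 296 rests.
- The 5% allowance may be generous, since a full baseline PRO assessment and complete frailty data are entry criteria. This narrows the gap, but 312 evaluable patients still give only 88.5%.
- The mismatch may be a rounding or log-hazard slip. That is plausible, and it is a reason to correct the stated figures.
- Fixed follow-up per patient is a legitimate design, described consistently, and gives a prognostic score one horizon. This stands. The common cut-off is an improvement and does not correct an error; estimates at 30 months remain available under it.
- The gain depends on accrual pattern, loss to follow-up and a fatigue effect that persists. This stands. Loss to follow-up or a weakening effect would reduce the gain, and neither was quantified.

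**Conclusion.** The concern holds in two linked parts. First, Sample size determination is internally inconsistent: under a two-sided 5% test its inputs need about 115 deaths (328 evaluable patients), while 296 at 35% gives about 104 deaths and 87% power. That is a modest shortfall of about 11 deaths and 3 percentage points of power. Second, as a separate design choice, ending survival collection at each patient's month 30 leaves up to 12 months of obtainable follow-up unused while the study is still open. A common closing date would bring expected deaths to about 114 to 124 and power to about 90% to 92%, with no more patients and no longer study. Those figures rest on 12-month accrual, 35% deaths at 30 months, no loss to follow-up and a constant fatigue hazard ratio, and they make no allowance for correlation with the adjustment covariates.

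**What to change.** 1. In Sample size determination, state the sidedness of alpha and the required number of deaths, and reconcile these with the hazard ratio and the sample size. If 296 and HR 1.11 are kept under a two-sided test with 35% events over 30 months, restate the power as about 87%. If the intended hazard ratio was nearer 1.116, say so.
2. In Study design and logistics and in Follow-up CRF, set the overall-survival cut-off at the calendar date on which the last enrolled patient reaches 30 months. Add one survival-status query at that date for each patient not known to have died (alive, dead with date, or date last known alive). Leave the PRO schedule and the existing forms unchanged.
3. State that contact after month 30 covers survival status only. Adverse events reporting runs to the last study-related procedure, and Serious adverse events reporting treats death as reportable within 24 hours. The text should therefore say whether those duties extend to the later query.

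The cost is extra data entry and a consent or ethics amendment, which has to pass at each participating centre in two countries and so is more than a minor wording change. The alternative is to keep the fixed 30 months and enrol about 346 patients (328 / 0.95 = 345.3, rounded up), which costs 34 more than planned.

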### Patient selection criteria

Inclusion criteria**:** 1) MM patients who have received at least 1 prior therapy and are considered as RRMM according to IMWG criteria; 2) adult patients (≥ 18 years old); 3) written informed consent provided, 4) patients who have been enrolled in other study therapy protocols (including investigational protocol treatments) are also eligible; 5) having a full baseline PRO evaluation completed, 6) all data available to calculate the frailty score.

Exclusion criteria: 1) having any kind of psychiatric disorder or major cognitive dysfunction hampering the provision of informed consent; 2) having reported any grade ≥ 3 adverse event within 2 weeks prior to study entry, 3) having received more than 5 prior lines of therapy.

### Recruitment strategies and data collection procedures

Eligible patients will be invited to participate, and consecutively enrolled, by their own treating physician at the participating center at the earliest convenience following local ethics approvals. Investigators will inform patients that participation in this study will not have any influence on their treatment choice and decisions. The number of eligible patients but not consenting to participate will be recorded by the Investigator. All eligible patients will be explained the purpose of the study and, those willing to participate, will be given written information sheet and will sign informed consent form. All consenting patients will be given a PRO Survey Booklet to be completed in the Hospital (baseline assessment). At subsequent pre-specified time points, patients may also complete the PRO Survey Booklet at home or alternatively in an interview conducted by phone.

A secure web-based data management tool will be used for which all study Investigators can upload data during the study period. A User ID and Password will be provided prior to the start of the study, so that all authorized study Investigators can access the web-based data collection system.

